#### Relatives

ICECAP Capability Measures (ICECAP-CPM)^32^ has been developed as a tool for use in economic evaluation conducted in an end of life setting for relatives. The questionnaire covers the attributes of: good communication, privacy and space, emotional support, practical support, being able to prepare and cope and being free from emotional distress related to the condition of the decent with the lowest score being 1 and the highest score being 5.EuroQoL-5D-5L.^26^Distress thermometer.^27^TechPH.^29^QFSSS.^30^HADS.^31^Care of the Dying Evaluation (iCODE)^33^ is a self-completion post-bereavement questionnaire, based on the key components of best practice in end of life care. It assesses quality of care for the dying through 32 main questions, reflecting core PC principles.

#### Volunteers

ICECAP-Adults (ICECAP-A)^34^ is a measure of capability for the general adult (18+) population for use in economic evaluation. The questionnaire covers the attributes of: attachment (an ability to have love, friendship and support), stability (an ability to feel settled and secure), achievement (an ability to achieve and progress in life), enjoyment (an ability to experience enjoyment and pleasure) and autonomy (an ability to be independent) with the lowest score being one and the highest score being 4.EuroQoL-5D-5L.^26^Distress thermometer.^27^Satisfaction with volunteering; Motivation (VFI)^35^ a 30 item measure of motivations to volunteer. Respondents answer each item on a 7-point scale ranging from 1 (not at all important/accurate) to 7 (extremely important/accurate).TechPH.^29^

#### Healthcare professionals

TechPH.^29^

Focus groups or in-depth interviews will be conducted with all groups at different stages of the study to assess the implementation of the study.

Process evaluation: Service Improvement Metrics: Process evaluation measures will be collected to assess the ‘success’ of the implementation process and how the service is being delivered. Data will be collected to assess the following: fidelity, dose and reach. Fidelity: Success of the Infrastructure. Dose: identification of patients, eligibility and take up of the service and whether the intervention was delivered as intended. Reach: (spread of implementation) quantifying the intervention implemented with the number of patients eligible for the service, number of patients who accept the service, number of wards with ‘eligible’ patients and number of wards where the service is implemented.

### Data collection and follow-up

The recruitment of the volunteers began in March 2021. When they finished their training, the new service started in September 2021 which was when patients/relatives recruitment started. Volunteer recruitment will be active during the whole study every 3 months. Recruitment is expected to end in September 2023.

The care teams offer the accompaniment of a volunteer to the patient/relatives. If they accept the accompaniment and participate in the study (if they want the accompaniment of a volunteer but do not want to participate in the study, the volunteer will be offered anyway). Once the informed consent to participate in the study has been signed, the data collection will proceed as described below. Further details can be seen in figure 1.

Patients/relatives who consent to participate (intervention and control group) will be invited to fill in at least three short questionnaires: at the time of recruitment for this study, 15 days after recruitment following the volunteer service experience (if hospitalised), and every month as long as the patient remains under PC care or until death. During the follow-up, patients and relatives will be asked if there is any change in their condition with respect to the questions asked at baseline. In this way, costly follow-up will be avoided. A maximum of 5 patients/relatives will also be invited to participate in an in-depth interview at various points during the implementation of the programme.

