### Settings

The study will be conducted in a palliative care unit from both a home care and an inpatient unit of the CUDECA foundation.

The hospitalisation unit is a small hospice consisting of 10 rooms where patients at the end of life are cared for in cases of uncontrolled symptoms, for family respite or in their final days, among other situations. In this unit, volunteers come every afternoon to the rooms where they wish to offer accompaniment to patients and their relatives.

In addition, CUDECA foundation provides home care to more than 1500 patients a year through 7 care teams made up of a doctor, nurse, psychologist and social worker. In these cases, the volunteer accompanies patients and relatives who wish them to do so.

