### Participants

A total of 140 patients and/or relatives will be selected from the home care and inpatient unit of CUDECA foundation where the ITV-Pal programme will be implemented. This sample size is enough to detect a mean difference of 3 in the HAD scores between groups of 25%, with a power of 80% and a confidence level of 95%.^24^ Sample size was adjusted according to the standard criteria for cluster randomised trials, using the design effect (DE) of 1.3. The DE was calculated as follows: DE=1+(nc–1)×ICC (where nc is the mean number of individuals in the cluster and ICC the intracluster correlation coefficient). The ICC in the present work was considered to be 0.05 and the mean cluster size was assumed to be 7. A potential loss of 20% was estimated. Therefore, 140 patients/relatives and 20 volunteers are required.

The inclusion criteria will be: patients and relatives cared for by a specialised PC team; to be over 18 years of age; consenting to participate in the study by signing the informed consent form. Subjects who have specific conditions reducing their physical ability to use the devices, for example, visual, hearing or motor impairments will be excluded from the study.

The HCP involved in these services will be included to measure the success of implementing the programme.

The inclusion criteria for volunteers will be an interview with the Volunteer Department and having completed basic care training to be able to carry out their work. Also, a commitment to participate in the study for 1 year. For this reason, more volunteers will be trained as needed during the 2 years of implementation.

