### Data analysis

#### Quantitative data

Intention-to-treat principle: Descriptive statistics will be used to summarise subject characteristics (age, gender, education, religion, socioeconomic status, marital status, place of residence) and the process evaluation. Basal comparison between groups for independent samples: Student’s t-test or χ^2^ test; for related samples: analysis of variance for repeated measures to analyse changes within groups. Multilevel analysis will be used for main and secondary outcomes. A multilevel modelling approach will be used to examine the difference in the primary endpoint between patients/relatives, taking account of clustering effects at volunteers level. All statistical tests will be two sided and considered significant if p<0.05. Repeated measurements of analyses of variance will be conducted to assess the development of endpoints over time. Multivariate Imputation will be used to handle missing data.

Also, outcome data will be collected for patients and relatives: the cost-effectiveness of care of dying patients, including the volunteer training programme, will be assessed by calculating the incremental cost-effectiveness ratio (ICER). The ICER is defined as the difference in total healthcare costs in the intervention group (including the costs of performing the intervention) compared with the total costs in the control group, divided by the difference in outcomes.^36^ Outcomes will also be measured as QALYs using the EQ-5D health-related quality of life questionnaire. We will also use the capabilities approach (ICECAP). The potential impact of the programme beyond the trial period will be extrapolated using modelling techniques.

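### The 15-day questionnaire applies only to hospitalised participants, so the repeated-measures ANOVA named for change over time does not fit the visit schedule; the planned multilevel model would

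*Protocol article*

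**What the plan says.** The Settings section places the trial in two kinds of care: "The study will be conducted in a palliative care unit from both a home care and an inpatient unit".

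Under Data collection and follow-up, consenting patients and relatives in both arms "will be invited to fill in at least three short questionnaires". The first is at recruitment. The second is "15 days after recruitment following the volunteer service experience (if hospitalised", where the bracket closes. The rest come "every month as long as the patient remains under PC care or until death". For further detail the section refers to Figure 1, which is not reproduced in the copy reviewed.

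Under Data analysis, Quantitative data, three statements bear on this schedule:
- "Multilevel analysis will be used for main and secondary outcomes", with clustering at volunteer level taken into account for the primary endpoint.
- "Repeated measurements of analyses of variance will be conducted to assess the development of endpoints over time". Repeated-measures ANOVA is also named earlier in the same paragraph, for changes within groups.
- "Multivariate Imputation will be used to handle missing data".

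The Randomisation section allocates volunteers in blocks of four and describes no stratification by setting.

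**The concern.** A conventional repeated-measures ANOVA compares the same set of occasions in every participant. The schedule as written does not supply one. Day 15 belongs to hospitalised participants only, and the number of monthly assessments depends on how long the patient stays in care or lives.

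If day 15 is entered as a level of the ANOVA, every home participant has an empty cell there. A complete-case ANOVA would leave them out. If the cell is instead treated as missing, the imputation would have only hospitalised participants' day-15 values to draw on. The Settings section says people are in the unit for uncontrolled symptoms, family respite or their final days, so they are a poor guide to participants at home.

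At stake is the description of how outcomes develop over time, where time since recruitment and place of care would be hard to separate.

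**Working it through.** **Inputs.** From Data collection and follow-up: baseline at day 0; day 15 if hospitalised; monthly thereafter. From Participants: 140 patients/relatives, mean cluster size 7, 20 volunteers. From Randomisation: blocks of four, two per arm. The home/inpatient split is not stated. I take a month as 30 days counted from recruitment, which is an assumption.

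**The plan's own figures.** The cluster count reproduces: 140 / 7 = 20 volunteers. Blocks of four give 20 / 4 = 5 blocks, hence 5 × 2 = 10 volunteers per arm.

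**Questionnaires due by time under care.** For time under care d in days, inpatient count = 1 + (1 if d ≥ 15) + floor(d/30); home count = 1 + floor(d/30).

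| Days under care | Inpatient | Home |
|---|---|---|
| under 15 | 1 | 1 |
| 15–29 | 2 | 1 |
| 30–59 | 3 | 2 |
| 60–89 | 4 | 3 |

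The first post-baseline measurement is therefore day 15 against about day 30. Three questionnaires are reached at about day 30 for an inpatient and about day 60 at home. The same section promises the minimum of three to everyone without this distinction, so the two statements sit badly together.

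**Records absent by design if day 15 were a common occasion.** Absent records = 140 × home share. With assumed shares of 25%, 50% and 75%: 140 × 0.25 = 35; 140 × 0.50 = 70; 140 × 0.75 = 105.

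**Reach into the arm comparison.** If a share h of an arm is at home, its mean day of first follow-up is 15(1 − h) + 30h = 15 + 15h. The difference between arms is 15 × (difference in h). With assumed imbalances of 10, 20 and 30 percentage points this is 1.5, 3.0 and 4.5 days. It is zero when the setting mix is equal, because the schedule itself is the same in both arms.

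**Analysis set against schedule.** The multilevel model named for main and secondary outcomes can use each measurement at its actual time. The ANOVA named for development over time cannot do so in its conventional form. The imputation sentence does not separate an assessment that was missed from one that was never due.

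**A further ambiguity.** The text does not say whether hospitalisation is judged at recruitment or on day 15. If on day 15, having that measurement depends on the participant's course after recruitment.

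**The case against.** The strongest reply is that the arm comparison does not rest on ANOVA at all. The article assigns main and secondary outcomes to a multilevel model and uses ANOVA only for within-group change and development over time. That stands, and it limits the point to those analyses.

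A reader might infer that the plan will impute a day-15 visit for home participants. The documents do not say so. The imputation sentence names no visit, and a visit never scheduled is not missing data in the ordinary sense. The ANOVA could also be run on monthly visits alone or within each setting. Imputation of day 15 is something the wording permits, not something it commits to.

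A reader might also infer bias between arms. The schedule applies to intervention and control alike, and nothing in the article shows an imbalance in setting. Only chance imbalance remains.

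Finally, a reader might infer that the family of a home patient who dies in the first month contributes nothing after baseline. The article gives no survival figure from which to size such loss, and relatives have a post-bereavement questionnaire (Relatives section).

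It is fair to add that the hospital condition is loosely worded, that Figure 1 may settle the schedule, and that visit windows, the primary time point and the detail of imputation can be left to a fuller plan. What remains does not depend on absent detail: the article itself fixes a setting-dependent schedule and names a method that needs a common one.

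**Conclusion.** The point holds in a limited form. On the plain reading, the first follow-up differs by setting (day 15 against about day 30), and so does the time needed to reach three questionnaires (about day 30 against about day 60). Repeated-measures ANOVA does not suit that schedule, nor follow-up that ends at death. If day 15 were made a common occasion, it would be absent for every participant not hospitalised: 35 to 105 of 140 over assumed home shares of 25% to 75%.

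The effect falls mainly on the over-time analyses. The arm comparison is affected only if setting happens to be unevenly spread across about 20 volunteers; an assumed imbalance of 10 to 30 points would move mean first follow-up by 1.5 to 4.5 days. The documents support no estimate of bias in the treatment effect. The conclusion rests on reading the bracketed condition literally and on months counted from recruitment. It is a modest defect that is almost free to correct.

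**What to change.** 1. In Quantitative data, replace the repeated-measures ANOVA with the multilevel model already planned, extended to three levels: repeated measures within participant, participants within volunteer. Include arm, actual days since recruitment and setting at recruitment as terms.
2. State that imputation is limited to assessments the participant was scheduled to have.
3. In Data collection and follow-up, reconcile the hospital condition on the 15-day questionnaire with the minimum of three for everyone. Say whether hospitalisation is judged at recruitment or on day 15, and make the text agree with Figure 1.

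The cost is a few sentences of analysis wording and a slightly more complex model. It needs no extra visit, and it does not require one month to be made the primary time point; that would be a trade-off, since it would take inpatients' day-15 data out of the primary comparison.

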**Figure 1 F1:**
[figure not shown]
Schematic of patient enrolment and data collection in the ITV-PAL study. Own elaboration. PC, palliative care.

Volunteers will spend 1 year accompanying patients in ITV-Pal. In the following year, there will be other newly trained volunteers joining the project. During their time, they will fill in five questionnaires: baseline, 3, 6 and 12 months following volunteering, and 3 months after. A maximum of five volunteers and five HCP with direct experience of the service will be approached for inclusion in in-depth interviews to explore their experiences during the implementation process and at the end of this study.

### Data analysis

#### Quantitative data

Intention-to-treat principle: Descriptive statistics will be used to summarise subject characteristics (age, gender, education, religion, socioeconomic status, marital status, place of residence) and the process evaluation. Basal comparison between groups for independent samples: Student’s t-test or χ^2^ test; for related samples: analysis of variance for repeated measures to analyse changes within groups. Multilevel analysis will be used for main and secondary outcomes. A multilevel modelling approach will be used to examine the difference in the primary endpoint between patients/relatives, taking account of clustering effects at volunteers level. All statistical tests will be two sided and considered significant if p<0.05. Repeated measurements of analyses of variance will be conducted to assess the development of endpoints over time. Multivariate Imputation will be used to handle missing data.

Also, outcome data will be collected for patients and relatives: the cost-effectiveness of care of dying patients, including the volunteer training programme, will be assessed by calculating the incremental cost-effectiveness ratio (ICER). The ICER is defined as the difference in total healthcare costs in the intervention group (including the costs of performing the intervention) compared with the total costs in the control group, divided by the difference in outcomes.^36^ Outcomes will also be measured as QALYs using the EQ-5D health-related quality of life questionnaire. We will also use the capabilities approach (ICECAP). The potential impact of the programme beyond the trial period will be extrapolated using modelling techniques.

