**Methods and analysis:**

A mixed-method study design will be conducted. We will recruit 20 volunteers and 70 patients in two years. Intervention: training of volunteers in new technologies and volunteer accompaniment of patients/relatives using technologies. The control group will accompany patients as usual.

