#### A: Quantitative approach

Pragmatic cluster randomised clinical trial to test efficacy (the unit of randomisation is the volunteer and the unit of analysis is the patient/relatives). A pragmatic cluster randomised controlled trial has shown to be the most appropriate design when the programmes are more focused on the organisational level.^22 23^ For our study, the cluster design is based on two levels: the higher or second level is represented by the volunteer (over volunteer the intervention is conducted, ITVPal Programme: Tech-Volunteer Programme in Palliative Care Services), and the lower or first level being represented by the patients/relatives, who have agreed to participate and are going to receive the tech-volunteer care from volunteers of ITVPal Programme.Before-and-after design for satisfaction of volunteers and HPC with the intervention and its implementation to test effectiveness. The design involves evaluating the effects of a deliberate intervention (introduction of ITVPal Programme) by comparing the outcomes of study participants investigated before the intervention with those measured afterwards.Cost–utility study from the perspective of the funder with a time horizon of 2 years. A detailed cost analysis including costs for the adaptation of a volunteer standard course to an ITVPal Programme as well as the recruitment and training costs of the volunteers will be performed.

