The implementation of this study has some limitations that we will try to control for and take into account. For example, in pragmatic cluster randomised controlled trials, the first bias to take into account is the selection bias, as the randomisation is usually applied in the second level, before recruitment of the first-level participants, which is where the intervention impact is measured. However, there are strategies that minimise this bias. First, the selection and follow-up of patients will be carried out by an external researcher who will have no knowledge of volunteer randomisation. Second, the effect of the intervention over recruitment can lead to different recruitment indexes, depending on the groups, due to the possibility that volunteers will be allocated a group in which they do not feel comfortable (eg, a volunteer who does not like the NT—technophobe—and will be allocated the intervention group) could be less motivated to participate. This issue will be taken into account in the analysis and it will be a result of the implementation process. There could be measurement bias due to mistakes in recording of some variables or interviewer bias due to the administration of the questionnaires. To minimise these biases, interviewers will have been trained previously to ensure that visits will be as homogeneous as possible. A data collection booklet and a manual that explains how each variable is measured will be designed.

Another bias that has already been mentioned is the involvement of volunteers in the year they will collaborate in ITV-Pal. For this reason, more volunteers will be trained. But also the number of patients/volunteers needed to achieve a representative sample and draw conclusions will be difficult to achieve in the 2 years of piloting the study.

Maybe the principal risk in this study will be that we will not be able to attend to the different needs of patients/relatives. In this case, we will try to adapt by offering other volunteers who may be able to give a better response to this need.

Due to the fact that in this study, we want to assess the implementation of an intervention programme, all these issues that we might find during the process could contribute to an improvement of the programme and would be useful for new research and the implementation of new interventions in the future.

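### Patients and relatives are pooled into one analysed population with no stated adjustment for role, so an unequal mix between arms could shift the primary comparison

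*Protocol article*

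**What the plan says.** The pooling appears at three points in the Protocol article.

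- **Design** (A: Quantitative approach): "the unit of randomisation is the volunteer and the unit of analysis is the patient/relatives", with "the lower or first level being represented by the patients/relatives".
- **Sample size** (Participants): "A total of 140 patients and/or relatives will be selected", and the calculation ends with "140 patients/relatives and 20 volunteers are required". No split, quota or pairing rule is given.
- **Analysis** (Quantitative data): the multilevel model addresses "the difference in the primary endpoint between patients/relatives, taking account of clustering effects at volunteers level". Volunteer is the only structure named, and no covariates are listed.

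Under Variables, HADS and EQ-5D-5L are given to both patients and relatives, so pooled scores are feasible. Randomisation allocates volunteers in blocks of four. The Discussion acknowledges that first-level participants are recruited after that step.

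**The concern.** Dying patients and their relatives may well have different average anxiety, depression and quality-of-life scores. When the two are analysed as one population, the arm comparison is protected from that difference only if the mix is the same in both arms or role is in the model. The article secures neither. The sample may contain any combination of the two, and randomisation acts on volunteers before participants are known.

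Three things are at stake:

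- If the mix differs by arm, part of the role gap appears as an arm effect, in either direction.
- If the mix is equal, the unmodelled role gap adds to residual variance and costs some power.
- If the programme's effect differs by role, the pooled figure is an average whose weights depend on who was recruited.

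**Working it through.** **Inputs from the article:** target difference 3 HADS points, power 80%, two-sided 0.05, ICC 0.05, mean cluster size 7, 20% loss, 20 volunteers, 140 participants.

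**Assumed, because the article gives no value:** SD about 5, a role gap of 1 to 4 HADS points, and various mixes by arm.

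**1. The plan's own figure.**
- Design effect: 1 + (7 − 1) × 0.05 = 1.3, as stated. Clusters: 140/7 = 20, as stated.
- The SD is not given, so 140 cannot be derived from stated inputs alone. With SD 4.95: 2 × (1.96 + 0.84)² × 4.95² / 3² ≈ 43 per arm, 86 in total; 86 × 1.3 ≈ 112; 112/0.8 = 140.
- An SD of about 5 is therefore what the stated sample implies, and it is used below.

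**2. Size of the bias.** Spurious arm difference = (role gap) × (difference between arms in the share of one role).

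| Role gap | 10-point mix difference | 20-point (60 v 40) | 40-point (70 v 30) |
|---|---|---|---|
| 1 | 0.1 (3%) | 0.2 (7%) | 0.4 (13%) |
| 2 | 0.2 (7%) | 0.4 (13%) | 0.8 (27%) |
| 3 | 0.3 (10%) | 0.6 (20%) | 1.2 (40%) |
| 4 | 0.4 (13%) | 0.8 (27%) | 1.6 (53%) |

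Percentages are of the 3-point target. Every entry is zero if the mix or the role means are equal.

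**3. Type I error.** Simulation of 2,000 trials with no arm effect: 10 + 10 volunteers, 6 participants analysed each (112/20 = 5.6, rounded up), volunteer variance 0.05 × 25 = 1.25, residual variance 23.75, role gap 3. Volunteer means were compared by a t-test on 18 df, with and without removing a fitted role effect.

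| Share of one role by arm | Without role: mean shift, type I error | With role: mean shift, type I error |
|---|---|---|
| 50% v 50% | about 0, 3.9% | about 0, 4.4% |
| 60% v 40% | 0.62, 8.7% | 0.02, 5.3% |
| 70% v 30% | 1.22, 20.0% | 0.01, 6.4% |

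**4. Power at equal mix.** A 3-point gap at 50:50 adds 3² × 0.25 = 2.25 to the residual variance, giving 26.0. With 5.6 analysed per volunteer, the SE of the arm difference is √[(2/10)(1.25 + 26.0/5.6)] = 1.086 without role, and √[(2/10)(1.25 + 23.75/5.6)] = 1.048 with role. On 18 df, power for 3 points is about 74% v 77%. Simulation gave 73% v 77%.

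**5. Chance imbalance.** With 56 evaluable per arm, a 50% share and design effect 1.3, the SE of the mix difference is √(2 × 0.25/56 × 1.3) = 0.108, or about 11 percentage points. With a 3-point gap, that is 3 × 0.108 ≈ 0.3 points of added noise in the arm difference.

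**6. Power for one role.** Suppose 70 are recruited, 56 evaluable and 3.5 per volunteer. Design effect = 1 + 2.5 × 0.05 = 1.125; effective number per arm = 56/1.125/2 = 24.9. With SD 4.96, SE = 4.96 × √(2/24.9) = 1.41, and power for 3 points is about 57%, against 80% for the pooled sample on the same basis.

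**The case against.** **Silence is not a decision.** A reader might infer that the plan has chosen a model without a role term. The article does not support that. It lists no fixed effects, and the sentence on the model does not name the study arm either. Model terms are commonly left to an analysis plan, which is not shown. This objection stands, so the point rests on the pooling that is written down.

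**The article does not predict a role imbalance.** The Discussion says the intervention "can lead to different recruitment indexes, depending on the groups". A reader might take this as an expected difference in patient/relative mix. In context it concerns volunteers who are uneasy with their allocated group and so less motivated. The same paragraph has participants selected by an external researcher unaware of allocation, and says the recruitment issue will be considered in the analysis. These safeguards make a systematic imbalance less likely. They do not remove chance imbalance, and they do not put role in the model.

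**The 140 may be 70 pairs.** The abstract says "We will recruit 20 volunteers and 70 patients in two years", which fits 70 patient–relative pairs. The mix would then be 50:50 in both arms and the mix bias would be zero. The Participants section does not say this, and its and/or wording permits other combinations.

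**Baseline adjustment would shrink the bias.** Questionnaires are also completed at recruitment. With an assumed baseline–follow-up correlation of 0.6 and a stable role gap, 0.6 points falls to 0.6 × (1 − 0.6) ≈ 0.2. The article does not state whether baseline is adjusted for.

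**A pooled average is a legitimate target.** Leaving out an arm-by-role term does not bias it. That the result describes neither group follows only if effects differ by role, which is not known.

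**Pooling is not wholly certain.** The only primary-outcome label is in the patients' instrument list, on EQ-5D-5L, whereas the sample size uses HADS. A patient-only primary analysis is conceivable, but the analysis section applies the primary endpoint to both groups.

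**Conclusion.** The point holds in a limited form. The article fixes one pooled patient/relative population for design, sample size and primary model, leaves the mix open, and states no adjustment for role. Randomising volunteers does not by itself guarantee a balanced mix.

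The harm is conditional. Under SD 5, ICC 0.05 and a 3-point role gap, none with a 60% v 40% mix documented except the ICC, the shift is about 0.6 points and type I error about 9%. At equal mix the cost is only about 3 to 4 percentage points of power, and with complete pairs there is no mix bias. The documents do not support saying that the trial will be biased, or that its authors expect the two arms to differ in role.

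The change is still worth making, because it removes the exposure at almost no cost.

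**What to change.** 1. In every pooled multilevel model of an outcome collected from both groups, include role (patient or relative) as a fixed effect.
2. Report the numbers analysed by role and arm.
3. Report the arm effect for patients and for relatives separately, with confidence intervals, as a secondary result for estimation only and without a claim of significance for either role.

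These should be written down before the analysis begins, so that the choice between pooled and role-specific results does not depend on the data.

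**Cost:** analysis wording only, since role is identifiable from the separate instrument sets. The main effect uses one participant-level degree of freedom and needs almost no extra participants. The role-specific intervals will be wide, in line with power of about 57% for 3 points in one role.
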